**Inclusion criteria**

1. Before starting any of the procedures specified in this protocol, informed consent forms must be signed by the patients.
2. Patients with untreated primary pterygium producing at least one of the following symptoms:
   1. Astigmatismo with no other cause.
   2. Foreign body sensation.
   3. Corneal affectation theatening the visual axis.
3. Age ≥ 18 years.

4. Able to comply with the treatment and the follow-up visits.

**Exclusion criteria**

1. Pregnant or lactating women, women in fertile age not following an anticonceptive plan.
2. Alergies to doxycycline or presence of other diseases where doxycycline might be contraindicated, such as lupus eritematosus or miastemia gravis.
3. Patients taking drugs that are incompatible with doxycycline or that reduce doxycycline efficacy.
4. Patients that can not be followed up regularly by psychological, social, familial, or geographical reasons.

Those patients excluded from the formal trial will be asked for permission (through informed consent) to use their excised pterygium tissue to establish cell cultures and perform additional cell and molecular biology studies.

**F.-** **Statistical analysis**

The variables that will be statistically analyzed are, on the one hand, the growth or reduction of the surface occupied by the pterygium lesion after the treatment as compared with that before the treatment. In addition, the recurrence percentage in both arms and the expression of genes and proteins in pterygium cells either treated or not with doxycycline will be analyzed. First, normalcy of distribution and variance of the data will be checked. If data are distributed normally and present homoscedasticity, comparison between both groups will be performed with simple tools such as Student´s *t* test. Otherwise, non-parametric tests will be used. Differences will be considered statistically significant when *p*<0.05. All patients that return to their second visit will be included in the analysis (intention to treat analysis).

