**B.- Clinical Trial Design**

The study has been designed as a unicentric trial, to be carried out at the Hospital San Pedro, Logroño (La Rioja), Spain. Two groups will be studied, one will receive doxycycline (2 daily doses, 100 mg each) for 30 days, while the other will receive a placebo. Patients will be randomly assigned to one of the two arms following a 1:1 proportion (treatment:placebo). Masking will be done using a double blind technique, so neither the patient nor the doctor will know who is receiving doxycycline or placebo.

To complete the study, each patient will be asked to attend 4 visits to the clinic, as follow:

Visit 1. Clinical history data will be collected and the lesion will be properly diagnosed. If the patient meets the inclusion criteria and does not fulfil any of the exclusion criteria, he/she will be asked to participate in the trial and sign the informed consent form. Consenting patients will be given a code for identification throughout the study. A photograph of the affected eye (or both in bilateral lesions) will be taken. The Pharmacy of the Hospital will provide the patient with a capsule bottle (randomly assigned to his/her study code containing either doxycycline or placebo) and the proper instructions to take the medicine together with instructions for following visits and telephone numbers for potential adverse affects.

If a patient needs to be excluded or does not consent to be included in the study, he/she will be asked for informed consent to use cells from his/her resected pterygium for experiments on cell and molecular biology. All regular procedures will be followed with these patients.

Visit 2. This will happen 31 days alter the first visit. The degree of compliance will be evaluated and the number of capsules that were not taken for any reason will be recorded. A second photograph of the affected eye(s) will be taken to compare with that taken in the first visit. The ophthalmologist will again evaluate the lesion and, depending on the stage of this lesion, a decision will be taken to remove it or not, following the usual protocols set in place by the Ophthalmology Service. If the pterygium is removed, the tissue will be sent to the CIBIR for cellular and molecular analyses.

Visit 3. It will take place 6 months alter the second one. The doctor will recognize the patient and record his/her observations. Particular care will be devoted to annotate any recurrences.

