**C.-** **Objectives and outcome endpoints**

The main objective of the study is to reduce pterygium growth with a pharmacological treatment and reduce the Lumber of cases that need surgical resection of the lesion.

As secondary objectives we look forward to:

1.- Determine whether treatment with doxycycline reduce recurrence rates in patients whose pterygium was surgically removed.

2.- Investigate which genes and/or proteins change their expression following treatment of pterygium cells with doxycycline.

To accomplish these objectives, a photograph of the lesion(s) will be taken Turing the first visit. After 30 days of treatment, a second photography of the same area will be taken. The surface occupied by the lesion will be calculated in both photographs using an image analyzing software package. The main outcome will be the ratio between the surface occupied by the lesion in the second photograph divided by the size in the first one (growth rate).

As secondary outcomes, we will analyze the recurrence rate at 12 months after the intervention and the genomic/proteomic expression of the resected pterygium.

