**E.-** **Patients**

**Total Lumber of patients**

There are 2 ways of calculating sample size to reach statistical significance in a clinical trial. The first one is a qualitative strategy where each patient is classified as a success or a failure to the treatment depending on whether their lesion size shrinks below a predetermined value (threshold). This allows a comparison between groups using a bilateral 2 for 2 independent samples. From the study of the disease we know that untreated pterygia keeps growing or maintains its size, but never tends to spontaneously reduce its size, so we can assume that the proportion of the placebo-treated group is asymptotically 0.0%. Depending of the power and the established threshold, the number of patients for each group are the following:

| **Power** | **Treshold at 25%** | **Treshold at 50%** | **Treshold at 75%** | **Treshold at 100%** |
| --- | --- | --- | --- | --- |
| 80% | 27* | 11 | 6 | 1 |
| 90% | 35 | 14 | 7 | 2 |

* Numbers indicate sample size on each group.

Secondly, we can also use a quantitative strategy where each patient receives a numeric value representing the percentage reduction (or growth) of his/her pterygium due to treatment. In this case, to detect significant differences in the null hypothesis contrast Ho:1=2 we will use a bilateral Student´s *t* test for 2 independent samples. If we assume that the mean reduction of the lesion in the placebo group is 5 % and in the doxycycline-treated group is 15 %, and that the standard deviation in both groups is a maximum of 15%, for a significance levels of 5%, the number of subjects is as follows:

| **Power** | **Number of patients per group** |
| --- | --- |
| 80% | 35 |
| 90% | 49 |

Since it is difficult to forecast the expected response, we have decided to follow the most stringent conditions and 98 patients will be recruited (49 treated with doxycycline and 49 treated with placebo). This sample size will allow to detect significant differences of 10% or higher in the diminution of pterygium size between the treated and the placebo groups. Besides, this number of patients will allow the qualitative analysis previously explained.

Recruitment will be performed among patients attending the Ophthalmology Service of the Hospital. Currently, 4 to 8 pterygium patients visit the Hospital every month.

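### A single per-test p<0.05 rule also governs the gene and protein expression search, so expected false positives grow with a feature count that the protocol does not state

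*Protocol*

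**What the plan says.** Section F (Statistical analysis) names three things to be analysed: the change in lesion surface, the recurrence percentage in both arms, and expression, of which it says "the expression of genes and proteins in pterygium cells either treated or not with doxycycline will be analyzed". One procedure follows for all of them. Normality and equal variance are checked; if they hold, "comparison between both groups will be performed with simple tools such as Student´s" t test, and otherwise by non-parametric tests. The criterion is then "Differences will be considered statistically significant when" p<0.05. Expression is not exempted, and no adjustment for multiple features is mentioned.

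Section C (Objectives and outcome endpoints) gives the second secondary objective as "Investigate which genes and/or proteins change their expression following treatment of pterygium cells with doxycycline", and the matching secondary outcome as "the genomic/proteomic expression of the resected pterygium". Section B says where trial tissue comes from: "If the pterygium is removed, the tissue will be sent to the CIBIR for cellular and molecular analyses". The protocol gives no assay platform, number of genes or proteins, or list of candidates for this analysis.

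**The concern.** A 5% threshold limits the error of one test. It suits lesion area, where there is one main comparison. It does not suit the question of which of many genes or proteins have changed. There the threshold is applied once per feature, and about 5% of the unaffected features will pass it by chance, however many patients contribute tissue.

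What is at stake is the reliability of the answer to a stated secondary objective. A list of changed genes or proteins drawn up under this rule would contain an unknown share of chance findings, and the reader could not judge that share without knowing how many features were tested.

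**Working it through.** **The plan's own figures.** The protocol states no figure for the expression analysis. Its only worked use of the 5% level is the sample size for lesion size in section E ("for a significance levels of 5%, the number of subjects is as follows"): mean reductions of 5% and 15%, standard deviation 15%, two-sided test. With n per group = 2(z₀.₉₇₅ + z_power)² × (15/10)²:

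- 80% power: 2 × (1.960 + 0.842)² × 2.25 = 35.3, so 36 (exact t test 36.3, so 37); stated 35.
- 90% power: 2 × (1.960 + 1.282)² × 2.25 = 47.3, so 48 (exact t test 48.3, so 49); stated 49.

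These agree to within two patients. The calculation concerns one comparison only and carries no allowance for, or information about, the expression search.

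**Inputs for the expression rule.**

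- Threshold per test: 0.05 (section F).
- Adjustment: none mentioned (sections C and F).
- Number of unaffected features, m: not given, so it is an assumption and a range is shown.

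**Formulas.** Expected false positives = 0.05 × m; this holds whether or not the features are correlated. Chance of at least one false positive, if independent = 1 − 0.95^m.

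| Unaffected features (assumed) | Expected false positives | Chance of at least one, if independent |
| --- | --- | --- |
| 10 | 0.5 | 40% |
| 20 | 1 | 64% |
| 100 | 5 | 99% |
| 1,000 | 50 | practically 100% |
| 4,000 | 200 | practically 100% |
| 20,000 | 1,000 | practically 100% |

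**Does sample size help?** No. In a simulation of 20,000 independent features with no true differences (50 runs at each sample size), unadjusted t tests gave on average 998 to 1,001 false calls per run. The average was essentially the same at 10, 25 and 49 patients per arm, and single runs ranged from 932 to 1,087.

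**Does adjustment help?** Yes. In the same simulation the Benjamini-Hochberg procedure at 5% gave on average 0.02 to 0.06 false calls per run. For a small panel, a Bonferroni threshold of 0.05/20 = 0.0025 brings the expected number from 1 down to 20 × 0.0025 = 0.05.

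**Share of the list that is false.** This needs two more assumptions: the proportion truly changed and the power per feature. Take 10,000 features and 60% power.

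- 1% truly changed: 100 × 0.60 = 60 true hits; 9,900 × 0.05 = 495 false hits; 495/555 = 89% false.
- 10% truly changed: 1,000 × 0.60 = 600 true hits; 9,000 × 0.05 = 450 false hits; 450/1,050 = 43% false.

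The share therefore depends heavily on inputs that the protocol does not supply.

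**The case against.** The strongest reply is that the protocol never says the p-values are raw. It gives a threshold and examples of tests and does not rule out adjusted p-values. Multiplicity handling for a laboratory outcome is often left to the SAP, which was not available here. This stands in part: the absence of adjustment is read from the text's silence. But section F is not silent on the criterion itself. It puts expression under the same test and threshold as the clinical variables, so an SAP that added a correction would be changing a rule that the protocol states.

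The second reply is that the breadth of the assay is unknown. This stands. A reader might infer from the words genomic and proteomic that a genome-wide assay is planned and that hundreds of false positives will follow. The protocol does not support that: it names no platform, and section A mentions a handful of factors (VEGF, versican, TGF, IL-6, IL-8) that would fit a small targeted panel equally well. Reaching about 200 false positives takes about 4,000 unaffected features; 1,000 give 50. Nor does the protocol support a claim that most listed genes would be false, since that share moves from 89% to 43% when only the assumed proportion truly changed is altered.

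A third stronger reading is that the expression result is distorted because only operated patients supply tissue. Section B does make removal depend on the stage of the lesion after treatment, so a comparison of resected trial tissue is made in a subset formed after randomisation. However, the objective in section C speaks of treating pterygium cells, and sections B, D and E provide for laboratory work on tissue from people outside the trial, with sections D and E naming cell cultures. The objective can therefore also be read as treated versus untreated cultures, where selection for surgery by arm would not apply. The point is a limit on interpretation for one reading, not a demonstrated bias.

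**Conclusion.** The point holds in a limited form. The protocol applies one per-test p<0.05 rule to an open search over genes and proteins, and that rule does not suit the search. The size is 0.05 times the number of unaffected features: below one false positive for 10 features, about 1,000 for 20,000. This rests on an assumed feature count and on taking the rule as written, without adjustment. Even at 20 independent features, the chance of at least one false claim is about two in three.

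The consequence is confined to a secondary laboratory outcome. The lesion-area comparison, the recurrence outcome and the sample size of 98 do not depend on it. It is worth correcting because the stated rule would give an unreliable answer to a stated objective.

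**What to change.** In section F, limit the plain p<0.05 criterion to lesion area and the clinical secondary outcomes. For expression, add that:

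- the number of genes and proteins measured will be stated;
- changes will be declared by false-discovery-rate control (for example Benjamini-Hochberg at 5% or 10%) across all features measured, or by a family-wise correction such as Bonferroni if only a small panel is used;
- the results will be reported as exploratory;
- where resected trial tissue is compared, the comparison covers operated patients only.

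Moderated t statistics are an option if a high-throughput platform is used, but are not needed for a small panel.

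The cost is a sentence or two and standard software, with no added patients, visits or assays. The downside is that fewer genes or proteins will be declared changed, and some true changes will be missed.

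### The analysis set labelled intention to treat is an available-case set, because it requires attendance at visit 2, which comes after randomisation

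*Protocol*

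**What the plan says.** Protocol section F (Statistical analysis) sets the analysis population: "All patients that return to their second visit will be included in the analysis (intention to treat analysis".

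The order of events is in section B (Clinical Trial Design). Allocation is 1:1, and at visit 1 the hospital pharmacy hands over a bottle that is "randomly assigned to his/her study code containing either doxycycline or placebo". Of visit 2 the protocol says: "This will happen 31 days alter the first visit". Compliance is assessed at that visit: "The degree of compliance will be evaluated and the number of capsules that were not taken for any reason will be recorded". No section removes a returning patient for missed capsules.

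Section C (Objectives and outcome endpoints) makes the main outcome depend on visit 2: "The main outcome will be the ratio between the surface occupied by the lesion in the second photograph divided by the size in the first" photograph. No other visit supplies the numerator.

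The protocol has no rule for a missing second photograph and no dropout allowance. Section E derives 49 patients per group at 90% power and recruits exactly 98.

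**The concern.** Intention to treat means that every randomised patient is analysed in the arm to which he or she was allocated. Its value is that the two groups compared are those that randomisation made. Attendance on day 31 comes after randomisation and after the whole treatment course, so it can be affected by the treatment and by how the lesion responds. A set chosen on that event no longer has the protection that the label claims.

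Two things are at stake. A report that follows section F would claim an intention-to-treat analysis that was not done. And if the patients who stay away differ in outcome from those who return, to a different extent in the two arms, the estimated difference and its p value are distorted. The protocol contains nothing that would show this or limit it.

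**Working it through.** **The plan's own figure.** Inputs from section E: difference 15 − 5 = 10 points, SD 15, two-sided 5%, 90% power. Normal approximation: n = 2 × (1.960 + 1.282)² × 15² / 10² = 47.3, so 48 per group. The exact t calculation gives 48.3, so 49. The stated 49 reproduces. The sample size is not the error, but it has no margin for loss.

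**Is the set intention to treat?** Randomisation is at visit 1 (section B). Inclusion is decided at visit 2, day 31 (section F). A patient randomised at visit 1 and absent at visit 2 is excluded. The set is a subset of those randomised, chosen on a later event, so the label does not fit. This needs no assumption.

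**How large could bias be?** All loss rates and patterns below are assumptions. Take no true effect, SD 15, 49 per arm, and a fraction f lost from one arm only, all from the half with less shrinkage. The mean of that half lies 0.798 × 15 = 11.97 points below the arm mean. Then:

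- shift in the returners' mean = 11.97 × f / (1 − f)
- SE of the difference = 15 × √(1/49 + 1/(49(1 − f)))
- two-sided error = P(Z > 1.96 − shift/SE) + P(Z < −1.96 − shift/SE)

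| f | shift (points) | SE | shift/SE | two-sided error |
|---|---|---|---|---|
| 10% | 1.33 | 3.11 | 0.43 | 0.063 + 0.009 = about 7% |
| 15% | 2.11 | 3.16 | 0.67 | 0.098 + 0.004 = about 10% |
| 20% | 2.99 | 3.21 | 0.93 | 0.152 + 0.002 = about 15% |

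The shift favours doxycycline if the loss is in the doxycycline arm, and placebo by the same amount if the loss is in the placebo arm.

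**Less extreme patterns.**

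- If 75% of the loss comes from the worse half, the shift is about half as large: 0.7, 1.1 and 1.5 points.
- Full selection in both arms, 15% doxycycline against 10% placebo: 2.11 − 1.33 = 0.78 points, and error of about 6%.
- Simulation with 20% doxycycline against 5% placebo loss, and a correlation of 0.3 to 0.5 between outcome and return: false gain of 1.1 to 1.8 points. Doxycycline wins falsely in about 5% to 8% of runs instead of 2.5%.
- Equal loss of the same kind in both arms (10% or 20%): no bias. Power falls from 90% to about 87% and 83%.

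**Would simple imputation repair it?** Take the 20% one-arm case in the doxycycline arm.

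- Imputing within arm, with no useful relation to baseline, gives the lost patients the returners' mean. The shift stays at 2.99 points.
- Drawing the missing values from the placebo arm gives 0.8 × 2.99 = 2.39 points.
- Setting missing ratios to 1 (no change) depends on the true course. If both arms shrink by 5%, the arm mean becomes 0.8 × (5 + 2.99) = 6.39, a shift of 1.39. If both arms grow by 5%, it becomes 0.8 × (−5 + 2.99) = −1.61 against −5, a shift of 3.39. That is more than among returners alone, and simulated error is about 22%.

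Section E supports either course: it says that untreated lesions grow or hold their size, and it also assumes a 5% mean reduction on placebo. In this illustration the lost patients lie 11.97 + 2.99 = about 15 points below the returners, so only an analysis over a range of values would cover the truth.

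**The case against.** The strongest reply is that the practical effect is likely to be small. Visit 2 is one month after visit 1. The entry criteria ask for patients able to comply and attend. The trial is double-blind, section D describes few and moderate adverse effects at this dosage, and the decision on surgery is taken at visit 2, which gives both arms a reason to return. All of this is fair. It makes the upper end of the table a near-worst case, but it does not make the label right, and screening before randomisation cannot prevent loss after it.

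Two stronger readings are tempting.

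- A reader might infer that this is an analysis of treatment completers, close to per-protocol. The documents do not support that. At visit 2, "the number of capsules that were not taken for any reason will be recorded", and nothing excludes a returner who missed them. Non-adherent patients who attend stay in.
- A reader might infer that the rule favours doxycycline, or that the p value must be wrong. The documents give no rate or pattern of loss, so the direction is unknown, and equal loss of the same kind leaves the p value intact.

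It can also be said that the choice of imputation method belongs in a statistical analysis plan. That is true of the method. It does not excuse the sentence in section F, which is in the protocol and fixes the set and its name.

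**Conclusion.** The point holds. The set in section F depends on a post-randomisation event, so the intention-to-treat claim is wrong as written, whatever the data turn out to be, and no other section repairs it. The correct name is available-case, or at best modified intention to treat.

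Bias is a conditional risk. It needs non-return that is related to outcome and differs between arms, and it may run in either direction. Under the assumed one-sided loss of 10% to 20% it amounts to about 1.3 to 3.0 points, against a planned difference of 10, with two-sided error of about 7% to 15%. Under milder or similar loss it is small or absent, and the main cost is power.

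**What to change.** Rewrite the sentence in section F along these lines:

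- The primary comparison is of all randomised patients, in their allocated arm.
- Patients who stop the capsules are still asked to attend visit 2 for the photograph. This prevents missing data and helps more than any imputation.
- Non-return and its reasons are reported by arm.
- Missing visit-2 ratios are handled under a stated assumption, with a sensitivity analysis over a range of values that may differ by arm, such as a tipping-point analysis or reference-based imputation from the placebo arm. A single imputed ratio of 1 should not serve as the conservative check, and within-arm imputation should not stand alone.
- The analysis of returners is kept as a secondary analysis, labelled available-case.

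The cost is a few sentences in section F, a little more analysis work, and possibly a slightly wider confidence interval. The details of the imputation can go in the statistical analysis plan.
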